### 2.6. Statistical Methods for Primary and Secondary Outcomes

#### 2.6.1. Primary Objective

The primary objective is to assess the performance characteristics of the symptom-based scoring system for the detection of radiation pneumonitis. An evaluation will be performed in patients available for assessment of the primary endpoint who have completed at least 10 questionnaires regarding their symptoms. To allow for patient-based analyses, the multiple score values documented for each patient over time will be reduced to one clinically relevant, patient-specific value only. Thus, for patients without radiation pneumonitis during the study, the maximum score value documented throughout the study will be used, and for patients with pneumonitis, we use the value documented at the time of diagnosis. These patient-specific values represent the fundamental units for all further statistical analyses. First of all, sensitivity and specificity will be estimated for every possible cut-off value of the symptom-based scoring system.

The ROC curve is used to graphically show the connection between sensitivity and specificity. ROC is defined as the plot of sensitivity versus 1-specificity (false-positive rate) across varying cut-offs. An ROC curve corresponding to greater discriminant capacity of the symptom-based scoring system is located closer to the upper left-hand corner. An ROC curve lying on the diagonal line reflects the performance of a diagnostic test that is no better than chance level. The AUC summarizes the entire location of the ROC curve. The AUC is an effective and combined measure of the sensitivity and specificity that describes the inherent validity of the usefulness of the test in general, where a greater area means a more useful test. If AUC = 1, the symptom-based scoring system is perfect in the differentiation between subjects with and without radiation pneumonitis. This happens when the distribution of the score values for the subjects with and without events do not overlap. In contrast, AUC = 0.5 means that the scoring system is performing no better than chance. Therefore, the AUC can be considered a valuable quantitative measure to prove the diagnostic ability of the symptom-based scoring system. A rough guide for classifying the accuracy of a diagnostic test is the traditional academic point system (AUCs of 0.5–0.6 = fail; 0.6–0.7 poor; 0.7–0.8 = fair, 0.8–0.9 = good and 0.9–1 = excellent). Therefore, any symptom-based score leading to an AUC of at most 0.7 will be rated insufficiently useful and is not considered worth pursuing.

Based on this definition, the following hypothesis system will be subjected to statistical analysis: H0: AUC = 0.7 versus H1: AUC ≠ 0.7.

Non-parametric methods for AUC estimation and testing using the normal approximation of the asymptotic properties of the AUC with standard errors derived by the DeLong, DeLong, and Clarke-Pearson method will be applied [24]. Technically, the SAS version 9.4 (SAS Institute Inc., Cary, NC, USA) LOGISTIC procedure with the ROCCONTRAST statement can be used to estimate the AUC and its 95% confidence limit and to provide the *p*-value for the test mentioned above. A significance level of two-sided 5% is prespecified. If the statistical significance of the AUC is reached, the most informative (optimal) scoring point to predict pneumonitis will be established. Based on discussions with experts, optimality is defined as a score cut-off value of at least 90% and specificity of at least 80%. In addition to this visual selection of a suitable cut-off value, the Youden index (sensitivity + specificity − 1) will be applied to propose an optimal cut-off value for further consideration [25,26].

Due to the limited sample size that could be realistically achieved in this multi-center trial within the given study duration, it was not considered feasible to develop and validate the optimal cut-off value identified within this single study at the same time by dividing the study population into training and validation cohorts. Therefore, the derived cut-off value should be considered a preliminary suggestion, which should be validated in subsequent studies. As a further sensitivity analysis, the relationship between tertiles of the symptom-based scores and the incidence of radiation pneumonitis will be statistically tested using the Jonckheere–Terpstra test, which is a nonparametric test for ordered differences among groups of score values [27,28,29]. It tests the global null hypothesis that the distribution of the response variable does not differ among tertiles. The test is designed to detect alternatives of ordered differences, meaning that the incidence of pneumonitis increases with the tertiles of score values. In addition, the impact of potential risk factors, including radiation dose, co-morbidity (particularly significant cardiovascular disease), history of smoking, radiation doses, and concurrent medication including chemotherapy and immunotherapy on the prevalence of pneumonitis, will be evaluated [4]. The histology of lung cancer (NSCLC or SCLC) was not associated with pneumonitis in previous studies and, therefore, its potential impact will not be separately analyzed [4,6,14].

Based on the participation of highly committed study sites only and our previous trial experience, the rate of missing data can be assumed to be rather low. Furthermore, the primary endpoint consists of the derivation of one patient-specific value from the multiple score values documented during each visit. Based on the scientific question of interest in this single-arm trial, missing values will not be imputed regardless of any intercurrent events (“treatment policy strategy”).

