### 2.4. Interventions

The patients receive the same radiotherapy or chemoradiation for lung cancer as they would have received without participation in the POLCAR trial. Radiotherapy is performed as volumetric-modulated arc therapy using conventional fractionation with doses per fraction of 2.0 Gy given five consecutive days per week and total doses ranging between 60 and 70 Gy [2]. The patients in this trial may receive any medical support required for adverse events, co-morbidities, or other conditions. Trial-specific interventions include completion of a paper-based questionnaire (symptom-based scoring system) once a week during and up to 24 weeks following radiotherapy and completion of a questionnaire rating the patient satisfaction with the symptom-based scoring system at the end of the radiotherapy course. The follow-up period of 24 weeks was chosen according to the results of previous studies showing that pneumonitis can occur up to 23 weeks following radiotherapy [4,5]. The English version of the questionnaire was properly translated into the languages of the participating centers.

The patients indicate and rate symptoms potentially caused by radiation pneumonitis, i.e., cough, dyspnea, and fever (Table 3), once a week by completing a paper-based questionnaire. During the radiotherapy course, the patients complete the questionnaire at the department of radiotherapy. After completion of radiotherapy, the information regarding the symptoms potentially related to pneumonitis will be obtained weekly by phone (to minimize hospital visits). The procedure of the telephone visits is clear, and uniformity is ensured. Support from caregivers is not allowed. Since the patients are contacted actively by staff members, the risk of loss to the follow-up is comparably low. In our previous trial, the rate of termination of follow-up due to the patient’s unavailability was 8.8% [6].

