If the total score is higher than at baseline prior to the start of radiotherapy, the patients receive a follow-up call after 3 days or are asked to present at the corresponding hospital. If pneumonitis is suspected, the patients undergo lung function tests. The suspected diagnosis of pneumonitis is considered substantiated in case of a decrease in forced expiratory volume in 1 s (FEV1) and diffusing capacity of the lung for carbon monoxide (DLCO) to less than 75% from baseline values [16,17]. In this situation, the patients receive a chest X-Ray (which may be supplemented by a computed tomography). Radiation pneumonitis is considered confirmed if opacities confined to the irradiation fields are seen on chest X-Ray and/or ground-glass opacities (focal or nodular), consolidation, or both are seen on computed tomography [18,19]. The imaging findings are interpreted by experienced radiologists. If the diagnosis of pneumonitis grade ≥ 2 (CTCAE v5.0) is made, the patients generally receive treatment with prednisolone [5,16,20]. If the symptoms are caused by a medical condition other than pneumonitis, the patients are treated for this situation. Finally, the total score of the symptom-based scoring system is correlated to pneumonitis (yes or no). Since the scoring tool is easy to use, consistent assessment across multiple centers appears secured. This assumption is supported by the experiences from a previous prospective trial [6].

At the end of the radiotherapy course, the patients will complete a questionnaire regarding their satisfaction with the paper-based version of the scoring system, modified according to the User Experience Questionnaire, a widely used and reliable tool [21,22]. If the dissatisfaction rate is >20%, the scoring system needs to be modified, and if the dissatisfaction rate is >40%, it is considered not useful. If patients withdraw their consent to participate in the trial, study-specific interventions are stopped. In case of adverse events, which do not allow patients to complete subsequent questionnaires, study-specific interventions are postponed or discontinued, if necessary.

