### 2.5. Sample Size Calculations

The main goal of this trial is to evaluate the usefulness of a new symptom-based scoring system with respect to the identification of elderly lung cancer patients developing pneumonitis after radiotherapy. The discriminative power of the symptom-based score will be assessed by calculating the AUC. The sample size is calculated to achieve acceptable precision in the estimation of the AUC measured by means of the 95% confidence interval by incorporating a pre-specified probability, which is referred to as assurance, of achieving the desired lower confidence limit [23].

The sample size calculations are based on a two-sided significance level of 5%, an AUC of 0.9, a pre-specified lower bound of the confidence interval of 0.7, an assurance probability of 80%, a ratio between negative and positive cases of 2.33 (70% of patients without and 30% with radiation pneumonitis). Based on these assumptions, 59 patients (18 with and 41 without radiation pneumonitis) are required within the Full Analysis Set. Assuming that 5% of patients will not qualify for the Full Analysis Set, a total of 62 patients should be enrolled. The drop-out rate includes patients who experience difficulties in completing questionnaires due to neurocognitive decline during the study period. The Full Analysis Set includes all the subjects who started radiotherapy.

A pneumonitis rate of 30% has been considered appropriate for the sample size calculation since, in a previous retrospective study investigating elderly patients irradiated for lung cancer, 27.3% of the patients developed pneumonitis [14]. Moreover, this rate is expected to be higher in the POLCAR trial due to the weekly assessment of pneumonitis for 24 weeks compared to the standard follow-up consisting of one visit about 6–8 weeks following radiotherapy only. All the lung cancer patients aged ≥ 65 years will be screened at each participating center. The recruitment of all 62 patients should be completed within 15 months. The treatment period will be 6–7 weeks, and the follow-up period 24 weeks. This equals a total running time for the trial of 22 months.

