## Figures and Tables

**Table 1 cancers-17-00807-t001:** Inclusion and exclusion criteria.

Inclusion criteria Histologically proven lung cancer Indication for radiotherapy or chemoradiation Mean radiation dose to ipsilateral lung >13 Gy Age ≥65 years Written informed consent Capacity of the patient to contract
Exclusion criteria Expected non-compliance Baseline score of >4 points, as these patients will likely not be able to tolerate the planned treatment, including the full radiation dose

**Table 2 cancers-17-00807-t002:** Schedule of enrolment, interventions, and assessments.

	Screening	Baseline	Weekly During RT	End of RT	Weekly Up to 24 Weeks After RT	End of Study
Informed consent and patient information	X					
Inclusion criteria	X					
Exclusion criteria	X					
Demographics	X					
Medical history and concomitant diseases		X	X	X	X	X
Concomitant medication		X	X	X	X	X
Systemic anticancer treatment		X	X	X	X	X
Physical examination		X				X
Telephone visits					X	
Performance status		X				
Pathology and tumor stage		X				
Upfront surgery		X				
Planned treatment		X				
Lung function test		X	X ^a^	X	X ^a^	X
Chest X-Ray and blood samples (inflammation parameters) ^b^			X ^b^	X ^b^	X ^b^	X ^b^
(Serious) adverse events			X	X	X	X
Treatment given as planned?			X	X	X	X
Symptom-based scoring system (paper version)		X	X	X	X ^c^	X
Satisfaction with the symptom-based score (paper version)				X		

RT = radiotherapy; ^a^ only in case of suspected pneumonitis; ^b^ only if the suspicions of pneumonitis are substantiated after lung function test; ^c^ by phone (telephone visit).

**Table 3 cancers-17-00807-t003:** Scoring points assigned to symptoms potentially associated with pneumonitis.

Symptom	Severity of the Symptom (as Stated by the Patients)	Points
Cough	No	0
	Yes, a little/sometimes	1
	Yes, moderate/regularly	2
	Yes, severe/permanently	3
Shortness of breath	No	0
	Yes, with intense exertion (e.g., climbing stairs)	1
	Yes, with mild exertion (e.g., walking on flat ground)	2
	Yes, at rest	3
Fever	No	0
	Yes, between 37.6 and 38.0 °C	1
	Yes, between 38.1 and 39.0 °C	2
	Yes, higher than 39.0 °C	3

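### The 10-questionnaire minimum is not tied to time after radiotherapy, so early leavers can count as non-cases with most of the risk window unseen, and an occasional confirmed case can be dropped

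*Protocol article*

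**What the plan says.** Section 2.6.1 defines who enters the primary evaluation: "An evaluation will be performed in patients available for assessment of the primary endpoint who have completed at least 10 questionnaires regarding their symptoms". The minimum, "completed at least 10 questionnaires regarding their symptoms", is a count of forms. It is the same for patients with and without pneumonitis, and it is not linked to time since radiotherapy. The availability condition in the first half of the sentence is not defined in the article.

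The same section reduces each patient to one score. A case contributes the score at diagnosis. A non-case contributes the highest score documented during the study. On missing data it states that "missing values will not be imputed regardless of any intercurrent events".

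Section 2.4 schedules the questionnaire "once a week during and up to 24 weeks following radiotherapy" and justifies that length because "pneumonitis can occur up to 23 weeks following radiotherapy". Where adverse events prevent completion of further forms, "study-specific interventions are postponed or discontinued, if necessary". Section 2.6.2 states that predictive values can be estimated without bias because the observed incidence reflects that of the target population.

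**The concern.** The status of a non-case is only as good as the time over which pneumonitis was looked for. A form count that is met shortly after radiotherapy does not secure that time. Two consequences follow from the text as it stands.

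- **Non-cases.** A patient who leaves soon after the tenth form can enter as pneumonitis-free. The patient's maximum is taken over few weeks and so tends to be low. Any later pneumonitis is counted as a true negative at low scores. Both effects tend to flatter specificity, AUC and negative predictive value.
- **Cases.** A case needs one value only, the score at diagnosis. If diagnosis comes before the tenth form and the forms then stop, the patient is left out although that value exists. Inclusion then depends on what happens after diagnosis.

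At stake are the performance estimates and, with 18 expected cases, which cut-off is called optimal.

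**Working it through.** **1. The plan's own figure.** Section 2.5 requires 59 patients (18 cases, 41 non-cases) for AUC 0.9, lower limit 0.7 and 80% assurance. Check: 1.96 × SE(AUC 0.7) + 0.8416 × SE(AUC 0.9) should be at most 0.2. The Hanley-McNeil variance at 18/41 gives SE(0.7) = √(4.4926/738) = 0.0780 and SE(0.9) = √(1.9344/738) = 0.0512. The sum is 0.1529 + 0.0431 = 0.196. The plan's 59 is reproduced, so 18 cases among 59 is a sound basis for what follows.

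**2. When the tenth form falls.** Section 2.5: "The treatment period will be 6–7 weeks, and the follow-up period 24 weeks". Table 2 adds a baseline score and an end-of-radiotherapy score, which may or may not be separate from the last weekly one. The end-of-study form is left out of the count.

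| Course | Extra forms counted (baseline, separate end of radiotherapy) | Forms by end of radiotherapy | Tenth form, week after | Follow-up weeks unseen | 10 as share of scheduled |
|---|---|---|---|---|---|
| 6 weeks | both | 8 | 2 | 22 | 10/32 = 31% |
| 6 weeks | one | 7 | 3 | 21 | 10/31 = 32% |
| 6 weeks | neither | 6 | 4 | 20 | 10/30 = 33% |
| 7 weeks | both | 9 | 1 | 23 | 10/33 = 30% |
| 7 weeks | one | 8 | 2 | 22 | 10/32 = 31% |
| 7 weeks | neither | 7 | 3 | 21 | 10/31 = 32% |

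These are the earliest times. Skipped forms move the tenth later.

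**3. True cases labelled non-cases.** Assumptions: onset uniform over weeks 1-23, loss uniform over weeks 0-24, independent of each other, true incidence 30%. A patient lost at week t (t ≥ 1) has onset still to come with probability (23 − t)/22. If only losses after week c enter the evaluation, the factor is (23 − c)²/(2 × 22 × 24):

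- c = 1: 484/1056 = 0.458
- c = 2: 441/1056 = 0.418
- c = 4: 361/1056 = 0.342

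Section 2.4 gives 8.8% loss through unavailability in the previous trial. Then 59 × 0.088 × 0.30 = 1.56, and the expected number mislabelled is 1.56 × 0.458 = 0.71 (c = 1), 1.56 × 0.418 = 0.65 (c = 2) or 1.56 × 0.342 = 0.53 (c = 4).

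The article gives no loss figure that includes death or illness. As an assumed range with c = 1-2, 15% loss gives 1.1-1.2 and 25% gives 1.8-2.0.

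**4. Cases dropped.** Under the same uniform onset, 18 × 1/22 = 0.8 cases are diagnosed by week 2. Only those whose forms then stop are lost: 0.8 × 0.088 = 0.07, or 0.8 × 0.25 = 0.2 if one in four stopped.

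**5. What one case can do.** Section 2.6.1 sets a 90% target, read here as sensitivity because the word is absent from the sentence. With 16 of 18 detected, sensitivity is 88.9% and the cut-off fails. If one of the two missed cases is dropped, 16/17 = 94.1% and it passes. If instead a detected case is dropped from 17/18 (94.4%), the result is 16/17 (94.1%), a change of 0.3 points.

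**6. Precision.** In a simulation with assumed binormal scores, AUC 0.9, 41 non-cases and DeLong variance, going from 18 to 15 cases lowered the chance that the lower limit exceeds 0.7 from 95% to 93% (Wald limits) or from 89% to 83% (logit limits). Losing one or two cases costs less than that, so the issue is bias rather than power.

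**The case against.** The availability condition that precedes the form count may be meant to require adequate follow-up, and its definition could sit in the full protocol or the SAP. That is possible, and the point is conditional on it. The only threshold the article fixes, however, is the count of 10.

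Follow-up is active. Patients are called weekly (Section 2.3), and Section 2.8.1 keeps follow-up going after termination, subject to agreement where the patient withdraws. This should hold loss down, but Section 2.4 itself reports 8.8% unavailability, and death and serious illness come on top.

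A reader might infer more than the documents support:

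- *That the rule regularly discards early severe cases.* Nothing says forms stop at diagnosis, Section 2.4 allows postponement, and the Discussion places onset often weeks to months after radiotherapy. The expected number is a small fraction of one patient.
- *That the form count causes the mislabelling.* It removes the earliest leavers and so reduces it: with no threshold the factor in step 3 would be 0.5, or 1.56 × 0.5 = 0.8 patients. The cause is counting leavers as non-cases. The count of 10 is simply too weak to prevent it.
- *That each lost case moves sensitivity by 1/18 = 5.6 points.* That is the extreme, reached when the dropped patient is the only missed case (17/18 to 17/17).
- *That the plan declares early leavers need no handling.* Section 2.6.1 says only that little missing data is expected and none will be imputed.

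Section 2.6.1 also calls the cut-off preliminary and in need of validation. That limits the consequences but does not remove the conflict with Section 2.6.2.

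**Conclusion.** The point holds in a moderate form. As written, and unless the availability condition excludes them, patients who leave shortly after radiotherapy count as non-cases with 20-23 of 24 follow-up weeks unobserved. The article's own rationale for 24 weeks and its claim of unbiased predictive values both speak against this.

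The expected size is below one patient: about 0.65-0.7 mislabelled cases among 59 at 8.8% loss with the tenth form at week 1-2, and more only if total loss is higher than documented. This rests on uniform, independent onset and loss and on 30% incidence. The direction tends to favour specificity, AUC and negative predictive value.

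Dropping a confirmed case is the lesser and rarer part. It matters because a single patient among 18 can decide whether a cut-off meets the 90% target. The findings do not support replacing the primary analysis: at 8.8% there would be about 59 × 0.088 = 5 leavers, too few to rest a weighted primary ROC on.

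**What to change.** In Section 2.6.1:

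- Include every confirmed case with a score at diagnosis, whatever the number of forms.
- For non-cases, replace the form count with a time criterion: observed without pneumonitis to, or close to, week 24.
- State what the availability condition means.
- Keep the one-value-per-patient DeLong analysis as primary.

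Keeping all cases but only fully followed non-cases raises the apparent incidence. For example, removing five leavers from the 41 non-cases moves it from 18/59 = 30.5% to 18/54 = 33.3%, which affects the predictive values. Two sensitivity analyses should therefore be reported. One treats early leavers as censored, with inverse-probability weights and death as a competing event. The other uses the protocol's 10-form set. The sentence in Section 2.6.2 on unbiased estimation should be qualified accordingly.

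The cost is a wording change and some extra programming, with no new visits, data or patients. A few early leavers no longer contribute to specificity, so precision falls slightly.

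### Section 2.6.1 forgoes in-study validation of the cut-off only because the sample cannot be split; a bootstrap needs no split and would correct, on average, a modest optimism in the reported sensitivity and specificity

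*Protocol article*

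**What the plan says.** All references are to the protocol article.

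- Section 2.6.1 reduces each patient to one score value, after which "sensitivity and specificity will be estimated for every possible cut-off value of the symptom-based scoring system".
- The primary test concerns the AUC: "H0: AUC = 0.7 versus H1: AUC ≠ 0.7". A cut-off is sought only if that test is significant.
- The cut-off is then chosen in two ways from the same data. One is a visual choice against a target of 90% (evidently sensitivity, though the word is missing) and 80% specificity. The other is the Youden index, which "will be applied to propose an optimal cut-off value for further consideration".
- On validation, section 2.6.1 says that the achievable sample does not allow the cut-off to be developed and validated "at the same time by dividing the study population into training and validation cohorts". It therefore labels the cut-off a preliminary suggestion and defers validation to later studies.
- Section 2.5 gives the size of the data set: "59 patients (18 with and 41 without radiation pneumonitis) are required within the Full Analysis Set".

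The article mentions no resampling method and no correction for choosing the cut-off on the same patients.

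**The concern.** A cut-off that maximises sensitivity plus specificity in a sample partly fits the chance pattern of that sample. The values read at that point are therefore too high on average, and more so for sensitivity here because it rests on only 18 cases.

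The plan sees that validation is needed, but the reason it gives applies to one method only. A bootstrap derives the cut-off from all patients and estimates the optimism of the selection from those same patients. The small sample is thus no ground for omitting it; a small sample is where optimism is largest.

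The score point is the trial's stated main goal (section 4) and a prerequisite for the mobile application (section 1). The sensitivity reported with it will shape expectations of how many cases the tool misses, and it will probably inform the design of the validation study. The label of preliminary warns readers about the score point but does not adjust the two numbers printed beside it.

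**Working it through.** **1. The plan's own sample size.** Inputs from section 2.5: two-sided 5%, AUC 0.9, lower limit 0.7, assurance 80%, ratio of non-cases to cases 2.33. I took the smallest number of cases *m*, with *n* = 2.33*m* non-cases, for which

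1.960 × SE(0.7) + 0.842 × SE(0.9) ≤ 0.9 − 0.7 = 0.2,

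using the Hanley–McNeil variance [A(1−A) + (m−1)(Q1−A²) + (n−1)(Q2−A²)]/(mn), with Q1 = A/(2−A) and Q2 = 2A²/(1+A).

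| Cases / non-cases | SE(0.7) | SE(0.9) | Sum |
|---|---|---|---|
| 17 / 40 | 0.0801 | 0.0526 | 0.2012 (too large) |
| 18 / 42 | 0.0778 | 0.0511 | 0.1956 (meets) |
| 18 / 41 (stated) | 0.0780 | 0.0512 | 0.1960 (meets) |

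The stated 59 is reproduced to within one patient, so 18 and 41 are used below.

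**2. Size of the optimism.** The article gives no score distributions, so these are assumptions: normal values rounded to the 0–9 scale, non-case mean and SD of 2/1.5, 2.5/1.5 or 3/2, the same SD in cases, and the case mean set so that the true AUC is 0.90. In each simulated trial the cut-off with the highest Se + Sp was selected. The apparent values were then compared with the true values at that cut-off.

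Middle setting (non-case mean 2.5, SD 1.5):
- Sensitivity: apparent 83.8%, true 80.4%; excess 83.8 − 80.4 = 3.4 points.
- Specificity: apparent 83.1%, true 81.6%; excess 83.1 − 81.6 = 1.5 points.
- Youden index: excess about 0.050 (0.034 + 0.015 before rounding).

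Across the three spreads the excess was 3.4 to 4.2 points in sensitivity, about 1.5 points in specificity and 0.050 to 0.058 in the Youden index. Other runs with somewhat different assumed distributions gave 0.040 to 0.050. The overall range is about 0.04 to 0.06.

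**3. Effect of the bootstrap.** In each resample *b*, drawn within cases and non-cases, choose the Youden cut-off k_b. Then

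optimism = mean over *b* of {[Se_b(k_b) + Sp_b(k_b)] − [Se(k_b) + Sp(k_b)]}, and corrected = apparent − optimism.

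With 300 resamples per trial, the middle setting kept +0.5 points in sensitivity and +0.3 in specificity (Youden index +0.008). The three spreads gave 0.008 to 0.012, so 80 to 83% was removed. Over all runs the remaining bias was 0.002 to 0.012.

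**4. When the 90%/80% rule is met.** At AUC 0.90, none of the three settings has a cut-off that truly reaches 90% and 80%. A sample cut-off does so by chance in about 10 to 14% of trials. The Youden index is then overstated by about 0.17 to 0.18, and the bootstrap removes only about 10 to 16% of this. At AUC 0.95 the excess in such trials is 0.080 to 0.102, and 23 to 29% is removed.

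**5. Stability of the chosen point.** In the middle setting, a cut-off of 4 or more has true Se/Sp of 0.887/0.748 (Youden 0.635), and 5 or more has 0.707/0.909 (Youden 0.616). The two nearly tie but trade off very differently. Depending on the assumed distributions, the truly best point is selected in about 47 to 72% of trials at AUC 0.90.

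**The case against.** The case on the other side is substantial.

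- **The limitation is disclosed.** The article calls the cut-off preliminary and uses the Youden index only to propose a value. This stands, and it lowers the weight of the point. It does not correct the figures reported with the cut-off.
- **The analysis plan is not shown.** A reader might infer that the results will certainly be published uncorrected. The document does not prove that: section 2.7 refers to a pre-defined analysis plan, which could contain a correction. What can be criticised is the stated reason, which treats the impossibility of splitting as settling the matter.
- **Neighbouring cut-offs will be visible.** A reader might infer that alternatives are hidden. They are not: sensitivity and specificity are estimated at every cut-off, the ROC curve is plotted, and section 2.6.2 adds predictive values for each score point. Values at a cut-off fixed beforehand, such as the 5 points from the earlier trial, carry no selection optimism. What is not shown is how often each point would be selected.
- **The primary test is untouched.** Testing the AUC against 0.7 involves no choice of cut-off. This stands in full.
- **The effect is small.** An excess of 3 to 4 points is less than one case in 18 (1/18 = 5.6 points). Correction hardly changes total error: the root mean squared error of the Youden index is 0.107 to 0.111 before and 0.106 to 0.107 after. This stands; the gain is in bias, not precision.
- **A visual choice cannot be bootstrapped.** This is true of the 90%/80% step as worded. The Youden step is an algorithm and can be repeated once ties are settled.

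**Conclusion.** The point holds in a limited form. The sample size justifies not splitting the cohort; it does not justify forgoing all validation within the study. At the planned AUC of 0.90 with 18 cases and 41 non-cases, the Youden-selected cut-off is reported on average about 3 to 4 points too high in sensitivity and about 1.5 points too high in specificity. The Youden index is too high by about 0.04 to 0.06, and a bootstrap reduces this to about 0.002 to 0.012. These figures rest on assumed score distributions, and 90% in the optimality rule is read as sensitivity.

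A reader might go further and infer that the bootstrap removes most of the bias whatever happens. It does so only when averaged over the selection procedure. If a cut-off meets 90%/80%, which is the result most likely to be promoted, most of the excess remains. The bootstrap also does not address the comparison of a maximum score in non-cases with a score at diagnosis in cases.

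Nor does it cure the imprecision from 18 cases: even 18 of 18 detected has an exact lower 95% limit of 81.5%. That is a matter of sample size and no part of this point. External validation remains necessary.

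**What to change.** In section 2.6.1, keep the full sample for derivation and the planned external validation, and add:

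1. Draw at least 1,000 bootstrap samples separately within cases and non-cases. Repeat the Youden selection in each, with a tie rule fixed in advance.
2. Report optimism-corrected sensitivity, specificity and Youden index beside the apparent values.
3. Report how often each score point is selected.
4. State that the correction holds on average, removes little of the excess when a cut-off happens to meet the 90%/80% rule, and supplements validation in later studies without replacing it.

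If the analysis plan already contains such a correction, section 2.6.1 should say so.

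The cost is a few lines of text and code, with no added patients or data. The downside is that the reported figures become slightly less favourable.
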